**II. Background and Rationale:**

While its expressions may vary, gender inequality is pervasive and persistent across time and place. There is growing recognition that gender norms significantly shape sexual behaviors and contribute to negative sexual and reproductive health outcomes among adolescents including sexual coercion, sexually transmitted infections, and early pregnancies. The qualitative research during the Phase 1 of the GEAS strongly suggests that patterns of gender norms structuring male and female behaviors reinforce gender unequal power dynamics during early adolescence. This process operates across numerous cultures and contributes towards maintaining patriarchal systems. The evidence suggests that such normative beliefs predispose to youth to subsequent gender-based violence, early school leaving, depression, and a host of negative sexual health outcomes, yet research lacks the measurement and longitudinal data to establish the temporality and strength of these associations. The GEAS is set to answer these questions using a longitudinal design and validated measures to explore these processes over time and across cultures.

Since initiating Phase 1 of the Global Early Adolescent Study nearly 4 years ago, awareness has grown globally that there is a need to focus on this age group both to understand the processes by which gender norms are reinforced and for the development of interventions that shift toward more gender equitable relationships.

The focus of the GEAS is on urban poor youth, a rapidly increasing population.

**III. Study Design**

**Overview of study design and methods.** The GEAS in Kinshasa will involve a quasi-experimental longitudinal (pretest-midline-posttest) design to compare changes in perceptions of gender norms and subsequent effects on adolescent health outcomes between a group of early adolescents receiving Save the Children’s GUG intervention and a non-intervention control group. The control group is an essential feature of the study and will allow the exploration of developmental changes in adolescent health in the absence of an intervention during this critical period of human development.

The selection of intervention and control groups, which will include a sample of both in-school youth (ISY) and out-of-school youth (OOSY), will be based on geography, school selection (the ISY samples), and self-selection of adolescents participating in the intervention activities, described in detail in Section IV, “Participants” below. All participants will complete a baseline survey (before the intervention begins) and will be surveyed every 6 months over a period of 5 years. The survey will be divided into 2 segments, each collected 6 months apart in order to collect a complete wave of data every year. Additionally, this approach will minimize respondent burden and minimize loss to follow-up due to frequency of contact. Starting with the second wave, the survey instrument will be modified to include questions appropriate for older adolescents, and at that time a supplemental IRB application/amendment will be submitted. Following the same procedure as in the Phase 1 pilot, data collection will be conducted by trained interviewers using mobile tablets with the capacity for face-to-face interview also known as CAPI (computer-assisted personal interview), computer-assisted self-interview (CASI), and/or ACASI (audio computer-assisted self-interview) survey administration. When CAPI is the primary administration method, CASI/ACASI will be used for potentially uncomfortable questions, such as those about adverse childhood experiences and sexual and reproductive health, in order to increase privacy and improve data quality. We will continue to use the secure survey design and data collection software (SurveyCTO) used during the Phase 1 pilot test, which greatly improves data security over other methods.

**IV. Participants**

The survey will take place beginning with 10-14-year-olds and their parents or caretakers (at baseline) in two urban poor communes in Kinshasa: Kimbanseke and Masina. What follows is a detailed description of study site selection, followed by descriptions of selection of parent and adolescent participants in both the intervention and control arms of the study.

*Study sites*

The survey will take place in two urban poor communes of the city of Kinshasa: Kimbanseke (population 946,000) and Masina (population 485,000), home to large populations of urban poor dwellers. Each of these communes is divided into neighborhoods (quartiers); Masina has a total of 21 quartiers, Kimbanseke has 46.

A mapping exercise conducted by Save the Children in May 2016 identified a total of 1,266 primary and secondary schools serving nearly 325,000 children located in the two communes. There are three main types of schools in Kinshasa: 1) public schools without religious affiliation, 2) public schools with religious affiliation, and 3) private/ religious schools. While each type of school attracts the lowest income populations, there is income diversity among the three types of schools, and more poorer children attend public schools compared with private. In consultation with KSPH researchers, Save the Children identified intervention and control neighborhoods in each commune based on equal representation of public schools and geographical divisions allowing a separation between intervention and control neighborhoods so as to minimize contamination.

*In-school sample*

Because a portion of the GUG intervention in-class and after-school activities, the selection of in-school participants will use a multistage cluster sampling approach to select at the first stage schools (clusters) based on geographical location and school type, and, subsequently, at the second stage, select adolescents from participating schools.

We will perform a random selection of schools in both the intervention zone and the control zone after stratification by commune and by school type, with unequal probabilities of selection based on school size. The school type strata are defined as follows:

1. Public non-religious schools
2. Public religiously-affiliated schools
3. Private religious schools

Table 1. Number of schools and enrollment

|  | **Masina** | | **Kimbanseke** | |
| --- | --- | --- | --- | --- |
|  | *Intervention*  *N=* | *Control*  *N=* | *Intervention*  *N=* | *Control*  *N=* |
| **Public, non-religious** | 9 | 5 | 16 | 1 |
| **Public, religious** | 20 | 14 | 24 | 41 |
| **Private** | 37 | 51 | 26 | 42 |

*In-school adolescent participants*

For both the intervention and control arms of the study, students will be invited to participate until 25 from each school assent (and whom have obtained parental consent). We will apply this predetermined cluster size to select the same number of students (n=25) per school in the intervention and control areas. Students in the control schools will be selected at random (from a list of all students between 10 and 14 years in the school), while those in the intervention area are self-selected based on their choice to participate in the intervention.

A total of 40 schools per study arm, equally distributed between Masina and Kimbanseke, will be selected. Altogether, 1,000 students will be enrolled in each school arm (intervention and control). Sample size calculation is detailed in the section, “Sample size and justification.”

*Parents of in-school adolescents*

All parents of in-school participants who consent their children to participate will be asked to participate in a baseline survey collecting sociodemographic information about themselves and household information.

*Out-of-school sample*

*Out-of-school adolescent participants*

Out-of-school participants will be recruited with the assistance of community-based organizations (CBOs) and religious organizations that work with OOSY in these communes. Specifically, KSPH will work with CBOs that serve out of school youth in each quartier and group (control or intervention) to create a list of eligible youth from which participants will be recruited. Youth whom have been out of school for 2 or more years will be prioritized due to the decreased likelihood that they will re-enroll in school during the study compared with youth who have been out of school for less time. A total of 400 out-of-school adolescents will be recruited in each arm of the GEAS cohort.

*Parents of out of-school adolescents*

All parents of out of-school participants will be asked to participate in a baseline survey collecting sociodemographic information about themselves and household information.

*Inclusion and exclusion criteria*

At the beginning of the study, youth aged 10-14 will be enrolled. In Kinshasa, it is not uncommon for a youth to live with a family other than their own either in hopes of broadening horizons or due to family dissolution or orphan status; and thus, youth living in foster families will be eligible to participate. However, where parents are available their consent will be sought. Where participants are orphaned, foster parent or guardian consent will be obtained. Homeless youth will not be eligible to participate due to the likelihood of difficulty with follow-up as well as involvement in intervention programming.

Table 2. Inclusion and exclusion criteria

|  | **Inclusion Criteria** | **Exclusion Criteria** |
| --- | --- | --- |
| **In-school youth** | Males and females between the ages of 10-14 years of age | Not between the ages of 10-14 |
|  | Lives within the geographic boundaries of Kimbanseke or Masina | Does not live within the geographic boundaries of Kimbanseke or Masina |
|  | Lives at home with a family (biological, adoptive, or foster) | Is homeless or lives on the street |
|  | Attends a school selected for the study | Attends a school not selected for the study, or does not attend school |
|  | Able to assent | Unable to assent |
|  | Has obtained informed consent from a parent or guardian to participate in the study | Has not obtained informed consent from a parent or guardian to participate in the study |
| **Parent/guardian of in-school youth** | Parent or guardian of an eligible in-school adolescent who has assented to participate | Not a parent or guardian of a participating in-school adolescent |
|  | Has provided informed consent to participate | Has not provided informed consent to participate |
| **Out-of-school youth** | Males and females between the ages of 10-14 years of age | Not between the ages of 10-14 |
|  | Lives within the geographic boundaries of Kimbanseke or Masina | Does not live within the geographic boundaries of Kimbanseke or Masina |
|  | Lives at home with a family (biological, adoptive, or foster) | Is homeless or lives on the street |
|  | Has not been enrolled in school for 6 or more months | Has not been enrolled in school for fewer than 6 months or is enrolled in school |
|  | Able to assent | Unable to assent |
|  | Has obtained informed consent from a parent or guardian to participate in the study | Has not obtained informed consent from a parent or guardian to participate in the study |
| **Parent/guardian of out-of-school youth** | Parent or guardian of an eligible out-of-school adolescent who has assented to participate | Not a parent or guardian of a participating out-of-school adolescent |
|  | Has provided informed consent to participate | Has not provided informed consent to participate |

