**In-school participants**

As described in Section IV, “Participants,” above, our intervention partners at Save the Children recently conducted a mapping exercise with guidance from KSPH researchers, the results of which have aided in our determination of recruitment sites.

Prior to study recruitment, the KSPH research team will inform the ministry of education, the ministry of health, and the national council for adolescent health “PNSA” (Plan National pour la Santé des Adolescents) about the schools and community organizations participating in the GEAS evaluation. The ministry of education will provide a signed letter for school directors acknowledging that the school has been selected to participate in the GEAS study.

- Control participants

Trained research interviewers hired by KSPH will visit each selected school in the control area to explain the research to them, and obtain their approval for their students to participate in the study. Working with the school directors, the KSPH team will establish a list of eligible students (10-14 years of age) attending the school in order to draw a random sample of 25 adolescents per school with replacement to participate in the longitudinal study. The school director will then organize a short meeting at the end of class with the eligible students to indicate that they have been selected for a study on gender and health in their community and that their parents will be informed about the study and invited for an information session at the school. The director will indicate to the students that their teachers will inform them about the time and place of data collection. Formal permission from school directors and community organizations (after-school programs, scout organizations, sports clubs for youth) will be obtained if data collection takes place in their facilities.

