Save the Children employs locally based intervention experts whom will take charge of recruitment of adolescents participating in the intervention by approaching schools within our target communes of Masina and Kimbanseke. Save the Children will establish a list of children participating in the intervention, and, of these, 25 will be randomly selected for participation in the study (if the intervention includes more than 25 students). Save the Children will facilitate the introduction of the KSPH team who will visit the school director of each selected school in the intervention arm to explain the GEAS research and obtain approval for their students to participate in the longitudinal study. School directors will provide the KSPH team with a list of all adolescents aged 10-14 years in the school in order to assess the potential selection bias of voluntary participation in the intervention (criteria for being in the intervention arm). Formal permission from school directors and community organizations (after-school programs, scout organizations, sports clubs for youth) will be obtained if data collection takes place in their facilities.

The process for recruitment of in-school intervention participants follows the same as that for in-school control participants, outlined above. Specifically, the school director will organize a short meeting at the end of class with the eligible students to indicate that they have been selected for a study on gender and health in their community and that their parents will be informed about the study and invited for an information session at the school. The director will indicate to the students that their teachers will inform them about the time and place of data collection.

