**Out-of-school participants**

- Control participants

KSPH will call upon standing relationships with community relays whom assisted in recruitment of participants in Phase 1 of the GEAS, along with staff from CBOs assisting with the recruitment of OOSY for the intervention, to create a list of eligible OOSY from which KSPH will recruit participants. As previously noted, youth who have been out of school for 2 or more years will be prioritized, then separating girls and boys and then sampling by age 200 adolescents from Masina and 200 from Kimbanseke.

After the sampling, KSPH will work with alongside RECOPE (Reseau Comunitaire de Protection de l'Enfant, child protection organization) members, who will facilitate house calls for KSPH researchers to meet with the parents of eligible adolescents. At those meetings, parents will be informed of the study goals and procedures and the risks and benefits of participating. In addition, they will be explicitly informed of their child’s confidentiality and of the procedures in place in the event of disclosure of abuse. At the end of the meeting, parents will be asked if they consent for their child to participate and if they themselves consent to participate in the baseline questionnaire. If parents give consent to both, they will be asked to complete the short (15 minute) questionnaire, either by themselves (CASI) if they can read and navigate a tablet on their own, or with the help of an interviewer (CAPI).

After parents have provided consent for their children’s participation, an appointment will be made for the adolescents will be informed and reminded by RECOPE members and other engaged community leaders regarding the time and place of data collection and its location (in a communal area such as a church or community building), which will be near their homes. A group of adolescents from the quartier will be convened, and the adolescents will be collectively informed about the study goals, procedures, and the consent procedure including the protocol for child abuse disclosure. At the end of the information session, children will have an individual conversation with his/her interviewer in order to assent to participate. After assent has been given, data collection will proceed.

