Initially at baseline descriptive analyses will be done to test for comparability of intervention and comparison groups. Subsequently bivariate statistics (Chi-Square and Student’s t-test) will be run exploring the relationships between independent variables and key outcomes. Finally multivariate analyses will be performed to evaluate associations between gender norms, empowerment and the primary outcomes of interest sexual behaviors and outcomes, gender based violence and mental health. Over time, tests of differences will be run exploring change in gender equitable attitudes, gender norms and how these changes predict changes in prevalence of gender based violence and contraceptive utilization between intervention and control groups.

5. Describe whether you are collecting or storing personal identifiers, and if yes, why you need them, and when and how you plan to dispose of them. Signatures on consent forms are considered to be identifiers.

Participants will be assigned a unique identifier, which will be recorded with their responses during electronic data collection. A separate document containing participant’s photograph, identification number, name, age, and location will be kept in a locked file cabinet at KSPH for data collectors to contact participants for follow-up. These will be retained with consent and assent forms in a dedicated and locked cabinet that will only accessed by the site PI and the study coordinator. All electronic data will be encrypted. All documents with contact information will be destroyed immediately following the last wave of data collection and only coded data without any identifiers will be retained.

6. Answer the following **if they are relevant to your study design**

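### In-school controls are a random draw from all pupils but intervention pupils are programme volunteers, and the planned comparison of changes removes only a fixed gap between them

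*Protocol*

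**What the plan says.** Section IV sets two selection rules for the in-school sample. For controls: "Students in the control schools will be selected at random (from a list of all students between 10 and 14 years in the school". For the other arm: "while those in the intervention area are self-selected based on their choice to participate in the intervention". Section V (Recruitment Process) repeats the difference. In control schools the research team lists all eligible pupils "in order to draw a random sample of 25 adolescents per school". In intervention schools the draw takes place only within the list of programme participants: "of these, 25 will be randomly selected for participation in the study (if the intervention includes more than 25 students".

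The protocol does not hide this. Section III calls the design quasi-experimental and names self-selection as one of the ways the groups are formed. Section V has directors of intervention schools supply a list of all pupils aged 10-14 so that the bias from volunteering can be examined. Section III compares changes between arms from a baseline taken before the programme starts. The analysis plan (Section V, item C.4) adds: "Initially at baseline descriptive analyses will be done to test for comparability of intervention and comparison groups".

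Schools are sampled within strata of commune and three school types, with probabilities based on size, giving 40 per arm split equally between the communes. The number per school type is not stated. Table 1 has the row "Public, non-religious | 9 | 5 | 16 | 1" (Masina intervention, Masina control, Kimbanseke intervention, Kimbanseke control).

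For out-of-school controls, Section V gives a rule: those out of school for two or more years first, "then separating girls and boys and then sampling by age 200 adolescents from Masina and 200 from Kimbanseke". The matching text for the intervention arm gives the same priority but is silent on sex and age.

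**The concern.** Objective 2 is to assess the impact of the programme. Pupils who choose to join a gender-norms programme may differ from the average pupil in motivation, parental support, age or sex, and any of these may affect later attitudes, exposure to violence and contraceptive use. An arm difference would then mix the programme's effect with the effect of being someone who joins. A larger sample does not help: it makes the biased estimate more precise.

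The stated responses describe the problem and do not resolve it. A baseline comparison shows whether the groups differ on measured items. The school list can compare volunteers with non-volunteers only on what it contains, and the protocol does not say that non-volunteers are surveyed. Item C.4 mentions multivariate analysis, but for associations of gender norms and empowerment with outcomes, not for the arm contrast. The sampling frames and the school allocation are fixed at enrolment, so a later analysis plan cannot recover them.

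**Working it through.** **1. What a comparison of changes removes.** Let the control mean be μ at baseline and μ + δ_all at follow-up. Let volunteers start at μ + g and, without the programme, change by δ_vol. Let the programme effect be τ.

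- Intervention change: (μ + g + δ_vol + τ) − (μ + g) = δ_vol + τ
- Control change: δ_all
- Difference in change: τ + (δ_vol − δ_all)

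The fixed gap g cancels; the difference in trajectory does not. The 13% contraception planning rate is for ages 15-17 (Sample size and justification), while enrolment is at 10-14. If baseline use is near zero in both arms (assumption), g is near zero too, and any volunteer difference lies in δ_vol − δ_all, where the comparison of changes cannot reach it.

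**2. The plan's own power, as a base for illustration.** Inputs: 13% against 26%, 40 schools per arm, ICC 0.2, two-sided alpha 0.05 (two-sided is assumed), with 10 girls per school in the text and 11 in Table 3.

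- Design effect = 1 + (m − 1) × ICC; effective n = 40m / design effect
- m = 10: 1 + 9 × 0.2 = 2.8; 400/2.8 = 142.9; power 79.5%
- m = 11: 1 + 10 × 0.2 = 3.0; 440/3.0 = 146.7; power 80.6%

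The stated 79% is reproduced to within 2 points.

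**3. Illustration with assumed gaps.** The documents give no volunteer gap, so the gaps below are assumptions. The results are the chance of a significant arm difference when the programme has no effect, in an unadjusted end-point comparison.

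- Contraception (m = 11, controls 13%): if volunteers would reach 15%, 17% or 20% anyway, the chance is 7.8%, 16% or 37% instead of 5%.
- Continuous score (40 × 20 per arm, ICC 0.15): design effect 1 + 19 × 0.15 = 3.85; effective n 800/3.85 = 207.8; standard error √(2/207.8) = 0.098 SD. Gaps of 0.05, 0.1 or 0.2 SD give 8%, 17.5% or 53%.

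For a comparison of changes, only the part of the gap that is a difference in trajectory counts.

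**4. School mix.** Table 1 counts, as public non-religious / public religious / private:

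- Intervention: Masina 9/20/37 (66 schools), Kimbanseke 16/24/26 (66)
- Control: Masina 5/14/51 (70), Kimbanseke 1/41/42 (84)

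Assume 20 schools per commune and arm, allocated in proportion to these counts:

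- Public, intervention: 20 × 29/66 + 20 × 40/66 = 8.8 + 12.1 = 20.9 of 40 = 52%
- Public, control: 20 × 19/70 + 20 × 42/84 = 5.4 + 10.0 = 15.4 of 40 = 39%
- Public non-religious, intervention: 20 × 9/66 + 20 × 16/66 = 2.7 + 4.8 = 7.6 of 40 = 19%
- Public non-religious, control: 20 × 5/70 + 20 × 1/84 = 1.4 + 0.2 = 1.7 of 40 = 4%

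An allocation with equal numbers per type would bring these gaps to zero. The text permits either. Matching on all three types is limited by the control zone: at most 5 public non-religious schools in Masina and 1 in Kimbanseke. Total public schools in Kimbanseke are close, at 40 and 42.

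**The case against.** The strongest reply is that this is a declared quasi-experiment. Self-selection is stated in three places, and the comparison of changes is a real safeguard that takes out any constant volunteer gap. Controls are not a pure random sample either: parental consent and assent apply in both arms, and families know their arm beforehand. Detailed modelling, such as covariate lists and weighting, commonly belongs in a statistical analysis plan, which is not shown. All of this stands. It means the authors did not overlook the issue, and the lack of a full model specification is not a fault of the protocol. It does not answer the point about trajectories, and the extra step of choosing the programme applies to one arm only.

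Four stronger readings are tempting, and the documents do not support them.

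- **A quarter-SD volunteer gap would equal the whole planned effect.** Table 3's 0.14 on Scale 1 is 0.14/0.59 = 0.24 SD, but it is a detectable difference. The text speaks of shifts of 10% and 20%. Read as shares of the mean of 3.99, these are 0.40 and 0.80, or 0.68 and 1.35 SD. The scale also serves a secondary outcome.
- **The arms will be 52% and 39% public.** This rests on the proportional-allocation assumption. Selection uses school size, which Table 1 as shown does not give. An unstated allocation is not an unequal one.
- **A difference in school type is a difference in poverty.** Section IV says more of the poorer children attend public schools, but also that every type draws from the lowest-income groups.
- **Out-of-school intervention youth are sampled without regard to sex and age.** The protocol is silent there, and silence does not establish a difference.

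**Conclusion.** The point holds for the in-school sample. The two arms use different sampling frames, and the comparison of changes corrects only for a constant difference between volunteers and average pupils. If their trajectories differ, the impact estimate for objective 2 is biased by that difference. A reader might infer that the bias favours the programme or is of a known size; the documents support neither. The error rates above show only how sensitive an unadjusted comparison is to assumed gaps.

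That the baseline helps little for contraception depends on low use at ages 10-14, which is an assumption. School-type imbalance is possible, at about 13 to 14 percentage points in the public share under proportional allocation, and avoidable. The out-of-school rule needs aligning as a matter of drafting.

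**What to change.** 1. Fix the school allocation: the same number per type and commune in both arms. In Kimbanseke, merge the two public strata, since only 1 public non-religious control school exists there. This balances the public share but not the religious split within it, so adjustment there should use public versus private. It needs no schools beyond the planned 40 per arm.
2. State that the objective-2 contrast is the between-arm difference in change, adjusted or propensity-weighted for baseline outcome, age, sex, commune, school type and the parent sociodemographic data already collected. Report the unadjusted result as supportive, and name residual self-selection as a limit on the causal conclusion. Model details can go in the analysis plan. Weighting costs some precision; the documents do not allow the amount to be calculated.
3. Optionally, ask control pupils at baseline whether they would join such a programme. This costs one question. Nothing in the documents shows that the answer identifies would-be volunteers, so it supports the adjustment and cannot replace it.
4. State one sex and age sampling rule for out-of-school youth in both arms. This is a change of wording if the same practice was intended.

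A more thorough alternative is to draw pupils at random from all eligible pupils in both zones and analyse by zone whatever the uptake. That removes the difference in frames, but it changes the question to the effect of offering the programme, and non-uptake would dilute the effect.
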